### Interim analyses {21b}

No interim analyses were planned.

### Methods for additional analyses (e.g., subgroup analyses) {20b}

Currently, there is no planned additional subgroup or adjusted analyses.

### Methods in analysis to handle protocol non-adherence and any statistical methods to handle missing data {20c}

The intention-to-treat analysis will be used, and the missing data will be handled appropriately following established guidelines [35].

### Plans to give access to the full protocol, participant-level data and statistical code {31c}

Any data required to support the protocol can be supplied on reasonable request to the corresponding author to promote study transparency. However, only de-identified datasets will be supplied.

## Oversight and monitoring

### Composition of the coordinating center and trial steering committee {5d}

The trial steering committee comprises three key members: one principal investigator and two co-investigators. This committee ensures the effective management of the trial. Duties encompass the approval of the final protocol and monitoring the ongoing progress of the study. The committee also has the authority to consider and agree upon modifications to the study protocol.

The trial management committee, comprising the two co-investigators, doctoral physical therapy students, and one independent primary investigator, is responsible for study planning and day-to-day management of the trial. The role of the group is to monitor all aspects of the conduct and progress of the trial, engage in the patient recruitment process, ensure that the protocol is adhered to, and take appropriate action to safeguard participants and the quality of the trial itself. The independent primary investigator will be responsible for generating the allocation sequences of the randomization. Meetings are held weekly.

### Composition of the data monitoring committee, its role and reporting structure {21a}

We will conduct the study without a Data Monitoring Committee. The principal investigator will organize and monitor the data obtained in this research project.

### Adverse event reporting and harms {22}

All participants will be carefully evaluated weekly, and all adverse events related to treatments will be reported, if any. The study related adverse events will be classified by the evaluator according to their severity as mild, moderate, or severe.

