**Methods/design:**

This study will be a randomized crossover trial. The participants for this study will be recruited from various places, including the University of Hartford, physical therapy clinics, and local businesses in the Hartford area, as well as online websites geared towards clinical trial recruitment. A total of 34 participants will receive all three treatments: active TENS, placebo TENS, and no treatment control. The treatment order will be randomized using a website-based randomization tool. For active TENS, a modulating frequency of 2–125 Hz will be applied with a variable pulse duration and maximal tolerable intensity for 30 min. The TENS will be left on for post-treatment testing to assess the effects during its maximally effective period for a total of 50 to 60 min. Furthermore, the intensity may be turned down if muscle twitching is present to ensure blinding of the evaluator. For placebo TENS, the unit will deliver current for 45 s, ramping to 0 in the last 15 s. The primary outcome will be pain intensity at rest and with movement, determined using the numerical pain rating scale. The secondary outcomes will be pressure pain threshold, heat pain threshold, temporal summation of pain, conditioned pain modulation, sit-to-stand test, and repeated trunk flexion. The assessments will be performed immediately before and after treatment. Statistical analysis of the data obtained will consider a significance level of *p* < 0.05.

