#### No treatment control

Participants will receive no TENS treatment but will perform a quiet rest period of 30 min instead of TENS. All other procedures will be the same. Therefore, this group will control for the placebo effect and repeated testing.

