## Assignment of interventions: blinding

### Who will be blinded {17a}

Both the evaluator and data analysts will be blinded to the randomization and intervention processes. The participants and the researcher responsible for the treatment cannot be blinded due to the nature of the interventions.

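### Adverse event reporting is limited to events judged related, in two unreconciled terms, so the no-treatment rate is likely to be understated and a comparison with it biased

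*Protocol article*

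**What the plan says.** The section Adverse event reporting and harms {22} of the protocol article has two sentences. The first sets surveillance and the reporting rule: "All participants will be carefully evaluated weekly", and "all adverse events related to treatments will be reported, if any". The second sets the grading: "The study related adverse events will be classified by the evaluator according to their severity as mild, moderate, or severe". Neither term of relatedness is defined, and the person who judges it is not named.

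Three other places bear on how the rule works:

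- The abstract (Methods/design) counts the control as a treatment: "A total of 34 participants will receive all three treatments: active TENS, placebo TENS, and no treatment control".
- The section No treatment control describes that session: "Participants will receive no TENS treatment but will perform a quiet rest period of 30 min instead of TENS". It adds: "All other procedures will be the same". The stated purpose is to control for placebo response and for repeated testing.
- The section Who will be blinded {17a} covers the person who grades severity: "Both the evaluator and data analysts will be blinded to the randomization and intervention processes". The researcher who applies the treatments is not blinded.

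**The concern.** The rule passes each event through a judgement of cause before it is reported. In a trial with a no-treatment session that otherwise runs identically, that judgement does work the design could do better. Algometry, heat testing, cold-water immersion, repeated sit-to-stand and repeated trunk flexion take place in every session. The participants have chronic back pain, so flares from testing are plausible in any of them. If every event were reported, the control session would show this background rate, and the TENS sessions could be read against it.

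Under a related-only rule, an event in a session without stimulation is easily set aside as unrelated to any treatment, while the same flare after stimulation may be kept. The two terms add to the difficulty. A flare from the cold pressor test is clearly related to the study but arguably not to a treatment, so the text does not settle whether it is reported. At stake is the trial's safety statement, not its efficacy result.

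**Working it through.** The article states no adverse event rate, count or harms comparison, so there is no figure to reproduce. The check is of wording, followed by an illustration on assumed rates.

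**Wording.**

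1. Reporting covers treatment-related events. Grading covers study-related events. If the second term is wider, some graded events are not covered by the reporting promise. If the two are meant as synonyms, the text does not say so.
2. No section commits to reporting events whatever their cause.
3. Because the control session includes all the other procedures, study-related events can occur there. Treatment-related events can occur there only if no treatment is itself counted as a treatment, as the abstract does.
4. The blinded evaluator grades severity. The text does not say whether the evaluator or the unblinded treating researcher decides relatedness.

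**Illustration: control session.** From the Sample size section, N = 34, or 34 × 0.85 = 28.9, about 29, after the 15% loss allowed for. Assumptions, not from the documents: a background probability r that a session has an event, and a share q of control-session events called related.

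Expected with all-cause reporting: N × r. Expected under the filter: N × r × q. Chance of at least one: 1 − (1 − r)^N and 1 − (1 − rq)^N.

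| r (assumed), N = 34 | All-cause: expected (chance of ≥1) | q = 0.5 | q = 0.25 | q = 0 |
|---|---|---|---|---|
| 2% | 0.68 (0.50) | 0.34 (0.29) | 0.17 (0.16) | 0 |
| 5% | 1.7 (0.83) | 0.85 (0.58) | 0.43 (0.35) | 0 |
| 10% | 3.4 (0.97) | 1.7 (0.83) | 0.85 (0.58) | 0 |
| 20% | 6.8 (0.999) | 3.4 (0.97) | 1.7 (0.83) | 0 |

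With 29 participants and r = 10%, the expected numbers are 2.9 with all-cause reporting, 1.45 at q = 0.5 and 0.73 at q = 0.25. The control rate is understated for every q below 1. It is zero only at q = 0, which the text does not force.

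**Illustration: TENS against no treatment.** Let TENS add a true excess e, let a share s of the events it causes be called related, and let q_T and q_C be the shares of background events called related in the TENS and control sessions.

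Reported difference = N × [e × s + r × (q_T − q_C)]; true difference = N × e.

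Apart from chance cancellation, the two agree only if s = 1 and q_T = q_C. With no true excess (e = 0), r = 10%, q_T = 0.5 and q_C = 0.25, the expected reports are 34 × 0.10 × 0.5 = 1.7 against 34 × 0.10 × 0.25 = 0.85. That is twice as many after TENS, produced by attribution alone. If q_T = q_C but s is below 1, a real excess is understated instead.

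**The case against.** The strongest reply is that the second sentence of the harms section rescues the first. Study-related naturally covers events from the test battery, the battery is run in the control session, and the abstract lists the control among the treatments. On that reading, control-session events can be reported and graded. This stands, and it limits the point. A reader might infer that the no-treatment rate is zero by construction. The documents do not support that, because they leave open which term governs reporting.

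A reader might also infer that harms cannot be compared between any of the conditions. That goes too far. Active and placebo TENS can each give rise to events called related, and they can be compared provided relatedness is judged blind by one rule. Nor does the text support the idea that events under placebo are less likely to be called related. That presumes that whoever decides relatedness knows the condition, and the text does not say who decides it.

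Three further replies deserve weight:

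- **No comparison of harms is planned, and harms are not among the listed outcomes.** True, but the trial will still make a safety statement by condition, and the rule shapes it.
- **The text restricts what is reported, not what is recorded, and weekly evaluation is provided.** Also true. The promise to readers nevertheless stops at related events.
- **A short article section leaves collection windows, form fields and tables to fuller documents.** That is fair for such detail, and its absence is not the point here. The point is a restrictive rule that is stated.

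Finally, the illustrative rates are hypothetical. A confidence limit for zero events in a sample this small would not measure the problem either, because it is the same under any recording rule.

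**Conclusion.** The point holds in a limited form. As written, the harms section applies attribution before reporting and uses two terms of different scope without reconciling them. Control-session events, including flares from the shared test battery, are therefore likely to be understated. A comparison of reported harms between TENS and no treatment would be biased unless every TENS-caused event is recognised and background events are called related equally often in both sessions. Nothing in the article secures either condition.

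The size cannot be fixed from the documents. On assumed background rates of 2% to 20%, with a quarter of control events called related, expected control events fall from between 0.68 and 6.8 to between 0.17 and 1.7 in 34 sessions. The direction for the control rate rests only on some control-session events being judged unrelated. The size of any bias in the comparison depends on attribution shares that nobody has stated. This is a minor safety-reporting correction, and the primary analysis is unaffected.

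**What to change.** Reword Adverse event reporting and harms {22} as follows:

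- Commit to recording and reporting all adverse events in all three conditions, regardless of cause.
- Record, as separate fields for each event, the condition that preceded it and a relatedness judgement. State who makes that judgement, preferably someone blinded to condition, and apply one rule throughout.
- Tabulate all events by condition, with relatedness shown as an attribute and not used as an entry filter.
- Use a single defined term in place of the two now in the section.

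The cost is a few lines on the session form and one table, with no change to sample size, visits or interventions. The small downside is that some unrelated events will be listed.

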### Trial design {8}

The study will be a crossover design and will be conducted at the University of Hartford. The study protocol was approved by the Institutional Review Board (IRB) of the University of Hartford, it was registered online on ClinicalTrials.gov, and will be reported according to CONSORT guidelines [16]. The protocol was developed following the recommendations of SPIRIT (Standard Protocol Items: Recommendations for Interventional Trials). The RCT will have a blinded evaluator.

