### Strategies to improve adherence to interventions {11c}

To minimize data loss, all participants will be guided when they sign the informed consent form and commit to attending on the scheduled treatment dates. Participants will receive an appointment card for scheduled sessions. An evaluator will be responsible for notifying and monitoring the participants weekly (via telephone contact, text message, and/or email) and accompanying them during the research. In cases of abandonment or impossibility of continuing the study, the data will be analyzed according to an intention-to-treat protocol.

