### Plans to promote participant retention and complete follow-up {18b}

The researchers will be in weekly contact with the study participants. Twenty-four hours before treatment sessions, a researcher will send text messages to remind participants of the treatment date and time. This procedure will ensure that participants receive the necessary attention and will assist in fully accompanying them during the research. If any participant fails to attend the appointment, the researchers will immediately call to inquire about the reasons for the no-show. If participants abandon the trial, the reasons will be recorded, the most recent data will be compiled, and analysis will be performed using the intention-to-treat principle.

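### The evaluator who must stay blinded also grades adverse events, and possibly makes the weekly contact, which opens an avoidable route to unblinding before later crossover sessions

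*Protocol article*

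**What the plan says.** All places are in the protocol article.

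- **Trial design {8}:** "The RCT will have a blinded evaluator".
- **Who will be blinded {17a}:** "Both the evaluator and data analysts will be blinded to the randomization and intervention processes". The next sentence adds: "The participants and the researcher responsible for the treatment cannot be blinded due to the nature of the interventions".
- **Adverse event reporting and harms {22}:** "All participants will be carefully evaluated weekly, and all adverse events related to treatments will be reported, if any". It continues: "The study related adverse events will be classified by the evaluator according to their severity".
- **Strategies to improve adherence {11c}:** "An evaluator will be responsible for notifying and monitoring the participants weekly".
- **Participant retention {18b}:** "The researchers will be in weekly contact with the study participants". The role is not specified.
- **Placebo TENS (under {11a}):** contrary to {17a}, this subsection holds that the placebo procedure blinds the person receiving it.

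**The concern.** The role that is to be kept ignorant of the intervention is also the role that receives and grades complaints about it. In a parallel trial with one assessment this might do little harm, because the event follows the measurement. Here every participant goes through active TENS, placebo TENS and no treatment in random order, so what the assessor learns about one session bears on the sessions still to come.

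Several outcomes leave room for assessor influence. Resting and movement pain are the participant's own ratings, but someone asks for them. Sit-to-stand and trunk flexion are timed, with a stopwatch named for trunk flexion. Pressure pain thresholds use a hand-held algometer, although software displays the pressure rate and the participant presses the button. If {17a} is right that participants are unblinded, a blinded assessor is the main remaining protection while these data are collected.

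**Working it through.** The plan states no figure on this point. The check compares the sections and then asks what a disclosure would tell the assessor.

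**1. Is it the same person?** Sections {17a} and {22} both refer to the evaluator with the definite article, and {8} promises one blinded evaluator. For adverse event grading, the overlap is explicit on the page. For weekly contact it is not: {11c} uses the indefinite article and {18b} speaks of researchers in general. Identity there is plausible but not established.

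**2. Can a report carry information about the condition?** There are two readings of participant blinding.
- Under {17a}, participants know their condition and can reveal it directly.
- Under the Placebo TENS subsection, they cannot tell active from placebo, but they still know which session was quiet rest. A complaint tied to the device then rules out no treatment for that session.

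The answer is yes on either reading; only the amount of information differs.

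**3. Do the existing safeguards close this route?**
- Participant timeline {13}: the envelope is opened after the assessor has left. This protects allocation.
- Active TENS (under {11a}): intensity may be lowered if twitching shows. This protects the testing period.
- Unblinding {17b}: the outcome evaluator may not break the blind. This does not govern what the evaluator is told.
- Study blinding assessment: the assessor's guess is recorded. This can detect unblinding but does not prevent it.

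None limits what the assessor hears through event reports.

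**4. What does a disclosure tell the assessor?** Write A for active, P for placebo and N for no treatment, and assume that all orders are equally likely. There are 3! = 6 orders: APN, ANP, PAN, PNA, NAP, NPA. With no information, each condition has probability 2/6 = 1/3 in any session.
- *Session 1 fully identified, say as A.* Two orders remain (APN, ANP). In session 2, A has probability 0, and P and N have 1/2 each. The same holds if session 1 was P or N.
- *Session 1 known only to have used a device.* Four orders remain (APN, ANP, PAN, PNA). In session 2, N has probability 2/4 = 1/2, and A and P have 1/4 each.
- *Two sessions fully identified.* One order remains and the third session is certain.

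**5. What cannot be computed.** The number of affected participants among the planned 34 is the product of the event rate, the chance that the event is reported before a later session, and the chance that the report is informative. The article gives none of these, so no bias estimate is possible.

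**The case against.** The strongest reply is that this is loose role wording in a condensed article, not a design defect. Much of it stands.

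- **Attribution.** A reader might infer that the evaluator decides whether an event is study related, which would call for knowledge of the treatment. Section {22} does not say so. It assigns severity grading only, and severity can be graded without knowing the condition. Grading by a blinded person is a defensible choice in itself.
- **Weekly contact.** A reader might take it as fact that the blinded assessor monitors participants each week. The wording of {11c} and {18b} does not establish that.
- **Telltale events.** It is tempting to say that skin redness or soreness would mark the active session. The article gives no event profile. The placebo unit looks identical and also delivers current, for 45 s, so a skin reaction could follow either device session.
- **The rise from 1/3 to 1/2.** This holds only when a report identifies a session completely. It measures how well later sessions can be guessed, not bias in the outcomes.
- **Timing.** The article does not say that grading precedes a participant's later sessions. Weekly evaluation in a three-session crossover makes it likely, but that is an inference.
- **Participant blinding.** The claim that assessor blinding is the main protection rests on {17a}, which the Placebo TENS subsection contradicts.

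The reply does not remove the explicit overlap between {17a} and {22}, or the absence of any rule on what the assessor may hear.

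**Conclusion.** The point holds as a risk of unblinding. As written, the blinded role receives adverse event information from participants who know at least which session had no TENS, and no safeguard covers that channel. A report can disclose or narrow a past condition and so inform guesses about later sessions. Full identification of one session raises each remaining condition from 1/3 to 1/2, and full identification of two settles the third.

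This rests on three assumptions: the evaluator in {22} is the outcome assessor, at least some reports arrive before the last session, and treatment orders are equally likely. The frequency is unknown. The text does not show that unblinding will occur, that grading requires it, or that results would be materially biased. It is best treated as a cheap improvement.

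**What to change.** Align {11c}, {18b} and {22} with {17a}:

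1. Assign between-session contact, and adverse event collection and grading, to an existing team member who does no outcome testing. For severity grading, prefer someone not told the condition; otherwise use the TENS allocator with severity definitions fixed in advance.
2. Alternatively, keep the roles but state that the outcome assessor receives no adverse event information about a participant until that participant's last session is complete. Someone else must then collect the reports in the meantime.
3. In either case, instruct participants not to discuss sensations or side effects with the assessor.

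The cost is a reassignment among existing staff and a few sentences of text. Treatment, sample size and analysis are unchanged. The one downside is that severity grading is unblinded if the allocator does it, which fixed definitions reduce but do not remove.

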### Frequency and plans for auditing trial conduct {23}

The principal investigator will permit study-related audits, and inspections by the IRB and applicable granting agencies or regulatory bodies, including access to all study-related documents.

### Plans for communicating important protocol amendments to relevant parties (e.g., trial participants, ethical committees) {25}

Any changes to the protocol will be reported to the IRB of the University of Hartford for approval.

### Dissemination plans {31a}

This trial's results will be presented at scientific conferences and published in a peer-reviewed medical journal.

